#### Participant timeline {13}

Study assessments at specific time points is presented in Table 1.

**Table 1 Tab1:**
[figure not shown]
Timeline of study

#### Sample size {14}

The sample size of this study was calculated according to the uniform standard of clinical trial report and the requirement of non-inferior experiment sample content. Experimental studies have shown that the minimum clinical significance value of WOMAC scale is 12%. Based on the previous research results of our research team, we set *σ* = 28%, *β* = 0.2, power = 80%, and significance level two-tailed *α* = 0.05. In order to prevent excessive loss of subjects, the shedding rate of 10% was calculated. A total of 120 subjects (27 per group, 4 groups, 10% shedding rate) were required. ITT analysis strategy will be adopted for data analysis. Paired *T*-test analysis will be performed on the evaluation data of OA patients before and after treatment, and variance analysis will be performed on the difference analysis among multiple groups.

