### Objectives {7}

The objective of this study is to assess the effectiveness and safety of utilizing LIFU, TENS, and LIFU combined with TENS after patients underwent PRP for treating KOA in this randomized controlled trial. We will evaluate how well this therapy worked for patients with KOA in terms of pain and physical function. After PRP treatment, it is hoped that the physical stimulation would help patients with knee osteoarthritis experience less pain and functional improvement.

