#### Assignment of interventions: allocation {16}

Randomization will be performed by simple randomization method using software-generated numbers before the study begins. Participants will be randomly assigned to one of the four groups in a ratio of 1:1:1:1. As the service will not release the randomization code until the patient has been recruited into the trial, which takes place after all baseline measurements have been completed, randomization will be completed by the staff member who not involved in the assignment or care of the trial participants will be used to assign participants to which group.

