## Discussion

Ultrasound and tens have been wildly used as safe and noninvasive physiotherapy for many years. Through the combination of TENS with ultrasound, patients can simultaneously receive ultrasound waves and electrical stimulation. Although PRP is now used for the treatment of KOA with excellent results, we hope that the physical stimulation can get better results after receiving PRP therapy. To our knowledge, there is no study using physical stimulation after PRP treatment. Therefore, we will conduct this randomized study to evaluate the LIFU, TENS, and LIFU combined TENS with PRP treatment on pain and function in patients with knee osteoarthritis. It is assumed that there will be a difference in outcomes between the intervention and control groups.

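### The sample size section names a non-inferiority requirement, but the objective, the add-on design and the planned tests all ask whether a device improves on PRP alone

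*Protocol article*

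**What the plan says.** Sample size {14} gives as its basis the uniform standard for trial reports and "the requirement of non-inferior experiment sample content". It then states that "the minimum clinical significance value of WOMAC scale is 12" per cent, sets the SD and error rates ("28%, *β* = 0.2, power = 80%, and significance level two-tailed *α* = 0.05"), and concludes: "A total of 120 subjects (27 per group, 4 groups, 10% shedding rate) were required". No non-inferiority margin, non-inferiority hypothesis or confidence-interval rule appears there or anywhere else in the article.

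The other sections point to superiority:

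- Objectives {7}: "it is hoped that the physical stimulation would help patients with knee osteoarthritis experience less pain and functional improvement".
- Discussion: "we hope that the physical stimulation can get better results after receiving PRP therapy", followed by "It is assumed that there will be a difference in outcomes between the intervention and control groups".
- Intervention description {11a}: all four groups receive the same three PRP treatments, and three groups receive a device in addition.
- Between-group tests: analysis of variance in Sample size {14} and the Kruskal–Wallis test in Statistical methods {20a}. Both test for a difference.

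**The concern.** In an add-on design with PRP in every arm, the useful question is whether the device adds anything. Non-inferiority to PRP alone does not answer it. A device with no effect is truly non-inferior, so a non-inferiority conclusion is compatible with zero benefit.

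The non-inferiority phrase in the sample size section is the only place where the article names a trial framework, and it contradicts the aim. What is at stake is how a null result may be described. Under the stated objective, a non-significant difference fails to show benefit. With a non-inferiority phrase already in the protocol and no margin fixed in advance, someone could choose a margin after seeing the data and present the same trial as having shown that the combination is not inferior.

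**Working it through.** **Inputs** (Sample size {14}): difference 12%, SD 28%, power 80%, two-sided alpha 0.05, 27 per group, 10% dropout. The article does not say what the percentages are taken of. I assume that both are on the same scale, so that only the ratio 12/28 = 0.43 matters.

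**1. The plan's own total.** 27/0.9 = 30 per group, and 4 × 30 = 120. The dropout step reproduces.

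**2. The 27 under superiority.** n = 2(z₀.₉₇₅ + z₀.₈₀)² × SD²/d² = 2 × (1.960 + 0.842)² × 28²/12² = 2 × 7.849 × 5.444 = 85.5, so 86 per group. One-sided 0.05 gives 68.

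**3. The 27 under non-inferiority.** With a margin of 12 (an assumption, since the plan states none), true difference 0 and one-sided 0.025, the formula is the same with the margin in place of d: 86 per group. One-sided 0.05 again gives 68.

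**4. Other routes.** A paired comparison gives 43 (two-sided) or 34 (one-sided). A four-group analysis of variance with a range of 12 between the extreme means gives about 60 to 120 per group, depending on where the other means lie. None gives 27. A non-inferiority calculation can be made to return 27 by adding a true benefit of about 9.3 to a margin of 12 (28 × √(2/27) × 2.802 = 21.3, and 21.3 − 12 = 9.3), but no such benefit is stated. The number therefore does not show which framework was used.

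**5. Power at 27 per group.** SE = 28 × √(2/27) = 7.62, and 12/7.62 = 1.575. By the normal approximation, power = Φ(1.575 − 1.960) = Φ(−0.385) = 35%. By the noncentral t (df 52, critical value 2.007) it is 34%. With Bonferroni for three comparisons it is 21%. At 30 per group without adjustment it is 38%.

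**6. How far apart the two claims lie.** This is an illustration only, with 12 taken as the margin (assumption), 27 per group, two-sided 0.05, noncentral t and one comparison with control:

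| True benefit | Superiority shown | Non-inferiority shown |
|---|---|---|
| 0 | 2.5% | 34% |
| 6 | 12% | 64% |
| 12 | 34% | 87% |

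**7. What the planned test does with inert devices.** With four equal groups of 27, the Kruskal–Wallis test was significant in about 4% of simulated trials (nominal 5%). The planned analysis therefore does not reward an inert device.

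**The case against.** The strongest reply is that the non-inferiority phrase has no operational effect. It is attached to no margin, hypothesis or interval rule, both between-group tests look for a difference, and the Discussion assumes one. The label does not change the number either: 86 per group follows from both frameworks when 12 serves as the difference or as the margin. This stands, and it limits the point to a contradiction in the stated framework and the latitude that it leaves.

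A reader might infer more than the document supports:

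- *That the plan would count an inert device as a success.* It would not. That needs a rule which nobody has written. Even with a margin of 12, one comparison with an inert device would fail to show non-inferiority about 66% of the time.
- *That the two-tailed alpha is itself at odds with non-inferiority.* It is not. Non-inferiority is routinely judged from a two-sided 95% interval.
- *That a 12% margin would accept a clinically relevant loss.* The plan calls 12% the smallest clinically significant value. Showing non-inferiority at that margin excludes losses of 12 or more, so what remains lies below the plan's own threshold.
- *That 27 per group was derived from non-inferiority.* Steps 2 to 4 show that this cannot be established.

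The reply does not remove the contradiction. The phrase is a positive statement in the protocol, not a detail left to a fuller document, and it cannot stand beside the objective.

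**Conclusion.** The stated design framework is wrong for this trial as written. A non-inferiority basis contradicts the aim of improving on PRP alone, the PRP-in-every-arm design and the planned tests of difference. The consequence is latitude in reporting and not a faulty decision rule.

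That latitude matters because non-significant results are likely. At 27 per group a single comparison with control misses a true difference of 12 about 65–66% of the time. This rests on the plan's own SD, on the two percentages sharing a scale, and on a pairwise comparison of means, which the plan does not name as its test. The non-inferiority probabilities in the table rest in addition on an assumed margin of 12 and only illustrate the gap.

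This should be fixed. The shortfall in power is the larger numerical defect in the same section, and correcting the label alone would leave it untouched.

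**What to change.** 1. Delete the non-inferiority basis from Sample size {14}. State that the trial tests superiority of each device arm over PRP alone.
2. Name one primary outcome and one time point. The Abstract makes the VAS pain score primary, while Outcomes {12} makes WOMAC primary. Neither singles out one of the follow-up times.
3. Specify the three comparisons with control, control them for multiplicity, and say how they relate to the global Kruskal–Wallis test in {20a}.
4. State that a non-significant difference will not be reported as non-inferiority or equivalence.
5. Restate the power for that comparison.

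Items 1 to 4 are wording. Their price is that a null result can no longer be presented favourably.

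Item 5 may cost more. With the stated inputs, 80% power needs 86 per group: 86/0.9 gives 96, or 384 in total. With Bonferroni for three comparisons it needs 114 per group: 114/0.9 gives 127, or 508 in total. If 120 patients is the ceiling, the protocol should say so and give the difference that can be detected with 80% power. At 27 per group and without adjustment for multiplicity, that is 7.62 × 2.802 = 21.3.

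If non-inferiority is really intended, the sponsor would have to state and justify a margin and a confidence-interval rule, and rewrite the Objectives and Discussion. The trial would then no longer address added benefit.

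### The stated inputs (12% difference, SD 28%, two-sided 0.05, 80% power) require about 86 evaluable patients per group, not 27; at 27 the power of one comparison with PRP alone is about 34%

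*Protocol article*

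**What the plan says.** Section Sample size {14} gives a complete set of inputs. On the effect, it says that "the minimum clinical significance value of WOMAC scale is 12" per cent. On the rest: "we set *σ* = 28%, *β* = 0.2, power = 80%, and significance level two-tailed *α* = 0.05". The SD is attributed to the team's own earlier results. For attrition, "the shedding rate of 10% was calculated". The conclusion is "A total of 120 subjects (27 per group, 4 groups, 10% shedding rate) were required".

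The same section says the calculation followed "the requirement of non-inferior experiment sample content". It names no margin. The Discussion states the opposite kind of hypothesis: "It is assumed that there will be a difference in outcomes between the intervention and control groups".

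On design and analysis, section Assignment of interventions: allocation {16} says: "Participants will be randomly assigned to one of the four groups in a ratio of 1:1:1:1". The sample size section names analysis of variance for the comparison among groups. Section Statistical methods {20a} names the Kruskal–Wallis test instead. Both are four-group tests for a difference. Section {20b} says that no adjusted analyses are planned.

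**The concern.** The standardised difference implied by the inputs is 12/28 = 0.43. An effect of that size cannot be detected with 80% power by comparing groups of 27, so either an input or the result is wrong.

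The trial asks whether adding LIFU, TENS or both to PRP improves outcome. If the printed inputs are right, a real benefit equal to the protocol's own minimum important difference would be missed about two times in three in any one comparison with PRP alone. A non-significant result would then say little, yet a reader relying on the claimed 80% power would take it as evidence that the add-on treatments do not help.

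The non-inferiority wording adds a second problem. For add-on treatments, being no worse than PRP alone is not the question the trial asks, and none of the planned tests addresses it.

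**Working it through.** **Inputs** (all from Sample size {14}): difference 12%; SD 28%; two-sided alpha 0.05, so z = 1.960; power 80%, so z = 0.842; dropout 10%. Allocation is equal over four groups (section {16}).

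**The plan's own figure.** The dropout step reproduces: 27/0.9 = 30 per group, and 4 × 30 = 120. The 27 does not.

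**Two-group comparison of means**

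n per group = 2 × (1.960 + 0.842)² × (28/12)² = 85.5, so 86. The noncentral t calculation gives 86.4, so 87. With 10% dropout, 86/0.9 = 95.6, so 96 enrolled per group and 4 × 96 = 384 in total.

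**Other readings of the same inputs**

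| Reading | n per group |
|---|---|
| Two-sample, one-sided 0.05 | 68 |
| Non-inferiority, margin 12%, true difference 0, one-sided 0.025 | 86 |
| Non-inferiority, margin 12%, true difference 0, one-sided 0.05 | 68 |
| Paired within-group test, two-sided | 43 (normal), 45 (t) |
| Paired within-group test, one-sided | 34 (normal), 36 (t) |
| Four-group ANOVA, means spanning 12% | 61 to 120, by pattern of means |
| Four-group ANOVA, one group 12% apart | 81 |
| Two-sample, Bonferroni for three comparisons | 114 |

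None gives 27. The closest, the one-sided paired test, does not compare groups.

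**Power at 27 evaluable per group, difference 12%, SD 28%**

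- One comparison with PRP alone, two-sided 0.05: 34.0% (t test) or 35.0% (normal approximation). If all 30 per group were evaluable: 37% to 38%.
- The same comparison at 0.05/3: 19.4%.
- Omnibus ANOVA, means 0, 0, 0, 12: the squared deviations from the mean of 3 sum to 9 + 9 + 9 + 81 = 108, so f = √(108/4)/28 = 0.186 and power is 32%. Other patterns with a 12% range give 22% (0, 6, 6, 12) to 42% (0, 0, 12, 12).

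**What 27 per group can support**

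- Standard error of a difference: 28 × √(2/27) = 7.62%.
- Difference detectable with 80% power: 7.62 × 2.802 = 21.3% (normal), or about 21.8% (t).
- Half-width of the 95% confidence interval for one pairwise difference: about 15%. The normal value is 1.96 × 7.62 = 14.9%; the t-based value is 15.3%.

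**What would have to change for 27 to give 80% power at a 12% difference**

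- The SD would have to be 12/(2.802 × √(2/27)) = 15.7% (normal), or 15.4% (t).
- Alternatively, adjustment for baseline would need a baseline–outcome correlation of about √(1 − 27/85.5) = 0.83. Section {20b} plans no adjusted analysis.

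**The case against.** The arithmetic is not in dispute. The best opposing argument is that other routes lead to or near 27, and that 34% describes one scenario only.

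- A non-inferiority calculation may assume a true benefit. With a 12% margin and SD 28%, 27 per group results from an assumed benefit of about 9.3% (two-sided 0.05: 21.3 − 12) or 6.9% (one-sided 0.05).
- If each modality added 12% and the effects were additive, the means would be 0, 12, 12, 24. ANOVA power at 27 per group would then be 74%, with 31 per group needed for 80%.
- The SD rests on earlier results that are not shown. The fault may be a misreported input rather than a real lack of power.
- Nothing in the planned analysis would let a finding of no worse than PRP alone count as success, so the non-inferiority phrase may be stray wording.

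Part of this stands. The pairwise 34% should be labelled as such, since the named analyses are omnibus tests. A misreported SD is possible, and the fix allows for it. The non-inferiority phrase changes no planned test. But the first two routes need an assumed benefit or a 24% spread of means, neither of which the document states, and the second still does not reach 80% at 27. Nor can the shortness of an article explain the gap: the inputs and the result are both printed, and they disagree.

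**Conclusion.** The concern holds. On the inputs as stated, the requirement is about 86 evaluable patients per group, roughly three times the 27 given (86/27 = 3.2). At 27 per group, power for a 12% difference is about 34% in one unadjusted comparison with PRP alone. It is 32% for the omnibus ANOVA if one group differs by 12%, against the claimed 80%.

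This assumes that 12% is the between-group difference to detect and that 28% is the SD of the analysed WOMAC measure in the same units. The document offers no other reading. The article does not say whether the percentages are of the scale or of change, but this does not matter here, because only the ratio 12/28 enters. The ANOVA figures are for the F test and were not recalculated for Kruskal–Wallis.

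The non-inferiority statement contradicts the two-sided alpha, the absence of a margin, the planned tests and the hypothesis in the Discussion. This must be corrected, because the sample size and power as printed cannot both be right.

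**What to change.** Rewrite Sample size {14} in one of two ways.

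1. If 12% and 28% are the intended inputs, keep 120 patients and describe the trial as a superiority design with 27 evaluable per group. State about 34% power for a 12% difference in one comparison with PRP alone, 80% power for about 22%, and an expected 95% confidence interval half-width of about 15% for each pairwise difference.
2. If the SD of the variable actually analysed is about 15.4%, print that SD, say which variable it belongs to and cite its source. The figure of 27 per group then stands.

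In either case, delete the reference to a non-inferiority calculation and name the comparison that the power refers to. State whether the percentages are of the scale or of change.

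The cost is protocol wording only, with no extra patients. Under the first option the stated power becomes less favourable.

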#### Recruitment {15}

A total of 120 patients will be enrolled in the study. Prior to recruitment, investigators will carefully question each patient’s medical history and study each patient’s laboratory and imaging tests. If the patient meets the inclusion and exclusion criteria, the investigator will assess the patient’s compliance and obtain an informed consent form (ICF) before collecting any data or performing any intervention. Patients will receive intervention within 48 h after initial assessment and randomization.

#### Assignment of interventions: allocation {16}

Randomization will be performed by simple randomization method using software-generated numbers before the study begins. Participants will be randomly assigned to one of the four groups in a ratio of 1:1:1:1. As the service will not release the randomization code until the patient has been recruited into the trial, which takes place after all baseline measurements have been completed, randomization will be completed by the staff member who not involved in the assignment or care of the trial participants will be used to assign participants to which group.

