**Methods:**

This is a protocol paper that outlines a randomized controlled trial, patients will be assigned randomly to the PRP group, PRP+LIFU group, PRP+TENS group, and PRP+LIFU combined TENS group. The patients will be followed at 12-week and 24-week time points to evaluate the primary and secondary outcomes of the study. The primary outcome is the VAS pain score. Secondary outcomes include Western Ontario and McMaster Universities Osteoarthritis Index (WOMAC) and International Knee Documentation Committee scores (IKDC). After baseline examination, all patients will sign a written informed consent for study participation after a full explanation of the treatment protocol. We have planned a total of 120 patients (30 patients per group).

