### Eligibility criteria {10}

Inclusion criteriaDiagnosis of osteoarthritis using the American College of Rheumatology criteriaRadiological grading of Grade I–III osteoarthritis (OA) of the knee using the Kellgren and Lawrence system

Exclusion criteriaPrevious internal and external fixation brackets after joint surgeryThe patients with local skin ulceration, infection, or local skin sensory disturbanceThe patients have used anti-inflammatory drugs in the past 2 weeks and non-steroidal anti-inflammatory drugs in the past 2 daysThe patients combined with language listening and speaking impairment or unable to cooperate with the doctor’s treatmentThe patients with a pacemakerThe patients with blood system diseases

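### Simple randomisation of 120 patients to four arms does not deliver the planned 30 per group; concealed permuted blocks would keep the arms close to it at almost no cost

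*Protocol article*

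**What the plan says.** The protocol article, Assignment of interventions: allocation {16}, names the method: "Randomization will be performed by simple randomization method using software-generated numbers before the study begins". It continues: "Participants will be randomly assigned to one of the four groups in a ratio of 1:1:1:1". The same section withholds the code until a patient has been recruited and baseline measurements are complete, and gives the task to staff outside the patient's care. Intervention description {11a} adds only that the sequence is computer-generated, with the same ratio. No section mentions blocks, stratification, minimisation or fixed arm totals.

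Two other places state group sizes. The abstract (Methods) says "We have planned a total of 120 patients (30 patients per group". Sample size {14} says "A total of 120 subjects (27 per group, 4 groups, 10% shedding rate) were required".

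**The concern.** A 1:1:1:1 ratio under simple randomisation is a statement about probabilities. Each patient is assigned independently, so the four arm totals vary by chance and only their expected value is 30. The article plans equal arms but names a method that does not produce them.

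What is at stake is precision in a trial with small arms that is run once. If one or two arms come out well short, comparisons involving them are less precise than planned, and no design feature limits how short an arm can fall.

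**Working it through.** **Inputs.** 120 patients, four arms, probability 0.25 each (allocation section); 30 planned per arm (abstract); 27 per arm and 10% loss (sample size section).

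**1. The plan's own figure.** 27 / (1 − 0.10) = 30 per arm, and 4 × 30 = 120. The dropout step reproduces. The 27 itself does not follow from the stated inputs (difference 12%, SD 28%, "power = 80%, and significance level two-tailed *α* = 0.05"): 2 × (28/12)² × (1.960 + 0.842)² = 85.5, so 86 per arm. That is a separate matter. Here 27 serves only as the plan's stated target.

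**2. Exactly 30 in every arm.** 120! / [(30!)⁴ × 4¹²⁰] = 0.00076, or about 0.08% (1 in 1,300).

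**3. Size of one arm.** Binomial(120, 0.25) has mean 30 and SD √(120 × 0.25 × 0.75) = 4.7. The central 95% range is 21 to 40. A named arm falls below 27 with probability 23%.

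**4. Smallest arm.** From 2,000,000 multinomial draws:
- some arm below 27 before any dropout: 77%
- some arm below 25: 46%
- median smallest arm 25, median largest arm 35, median gap 11

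With independent 10% loss, the median smallest evaluable arm is 22 under simple randomisation and 25 if exactly 30 are randomised to each arm. Fixed arms therefore do not guarantee 27 evaluable either, but they come closer.

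**5. Precision of a pairwise difference.** Variance ratio = (1/n₁ + 1/n₂) / (2/30). Two examples:
- arms of 25 and 35: (0.0400 + 0.0286) / 0.0667 = 1.03
- arms of 25 and 25: 0.0800 / 0.0667 = 1.20

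Over simulated allocations, for a given pair, the mean ratio is 1.027 and the 95th percentile is 1.21.

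**6. Power.** If power were truly 80% at 30 per arm, power at a given variance ratio (VR) is Φ(2.802/√VR − 1.960). VR = 1 gives 80%. Averaged over simulated allocations the result is 79.0%, with a 5th percentile of 72.2%. At the article's own 12% and 28%, power is 38.2% with 30 per arm and averages 37.6% under simple randomisation.

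**7. With permuted blocks.** If complete blocks add up to 120, every arm has exactly 30. With random blocks of 4, 8 and 12 the last block may be incomplete:
- 112 patients in complete blocks give 28 per arm. The other 8 come from a block of 12 with at most 3 per arm, so arms lie between 28 and 31.
- 116 patients in complete blocks give 29 per arm. The other 4 add at most 3 to any arm, so arms lie between 29 and 32.

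No arm starts below 28.

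**The case against.** The strongest reply is that simple randomisation is a valid method whose chance imbalances are already covered by the test's error rate, and that the average loss is about one point of power. This stands. It also holds for the planned overall comparison of four groups: ANOVA power calibrated to 80% at 30 per arm averages about 79% under random arm sizes. The striking probabilities describe arm counts, not power.

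Second, 27 is a weak threshold because the stated inputs do not produce it. This also stands. A reader might infer from the 77% that most realisations would turn an adequately powered trial into an underpowered one. The documents do not support that, since on their own inputs power is low even with exactly 30 per arm. The 77% shows only that the method misses the plan's own number.

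Third, in an open-label trial simple randomisation is the least predictable method. This is true, but randomly varying, concealed block sizes limit the predictability, and the article already withholds the code until after baseline.

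Fourth, the authors may have meant a pre-generated list with 30 places per arm, loosely called simple, or the full protocol may specify blocks. The figures above would then not apply, but the article would name the wrong method and still need correcting.

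A reader might also infer that disease severity will be unbalanced and left uncorrected. The documents do not carry that. Eligibility {10} uses Kellgren-Lawrence grade ("grading of Grade I–III osteoarthritis (OA) of the knee using the Kellgren and Lawrence system") only as an entry criterion. The article gives neither its prognostic strength nor the share of each grade. Methods for additional analyses {20b} says that adjusted analyses are not currently planned, which is not an exclusion. Equal arms would in any case barely change baseline imbalance: for a continuous score, some pair of arms differs by 0.5 SD or more in 22% of simple randomisations and in 21% with fixed arms of 30.

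**Conclusion.** The point holds as a mismatch between the named method and the planned group sizes. It is not a finding of bias. The plan will almost never give 30 per arm, and the typical smallest arm is 25. The average cost in precision is small; the reason to act is the poor tail, where a given pair of arms loses 21% or more in variance in about 1 trial in 20, and where the loss is avoidable. The arm-count figures assume independent assignment at probability 0.25 and exactly 120 patients. The power figures also assume that power would be 80% at 30 per arm, which the article's own inputs do not support. This is a worthwhile correction of moderate weight.

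**What to change.** In Assignment of interventions: allocation {16}, replace simple randomisation with computer-generated permuted blocks of randomly varying size in multiples of four (for example 4, 8 and 12). State that block sizes are unknown to recruiting staff. Keep the release of the code after baseline as already planned. If a list with 30 places per arm was intended, describe that list instead.

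The cost is one new list from the same software before the first patient is allocated. The small downside is some predictability at block ends in an open-label trial.

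Stratifying by Kellgren-Lawrence grade is optional. Imaging is already reviewed before enrolment, so the grade is available in time. Carrying the stratum into the analysis would cost more than a new list, because the Kruskal–Wallis test in Statistical methods {20a} takes no covariate and would have to be changed.
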